### Oversight and monitoring

#### Composition of the coordinating center and trial steering committee.

The lead researcher (*SS* in the authors’ list) responsible for the study’s design will supervise the trial and manage the project as a whole. As the trial progresses, any necessary corrections will be addressed through decisions made by the entire committee (all authors).

#### Data monitoring.

**Harms:** No adverse events are anticipated, aside from potential temporary minor discomfort or fatigue. Therefore, a data monitoring committee will not be established. However, should any serious adverse events occur during the trial, the principal investigator would promptly report them to the Ethics Committee of the Faculty of Medicine of Monastir (Tunisia).

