### Eligibility criteria

Inclusion criteria will be the presence of a chronic NP lasting for more than three months, and a PI-NRS pain level at baseline assessment ≥ 3. Non-inclusion criteria will be acute NP, specific causes of NP (***e.g.,*** chronic inflammatory diseases), spine trauma or surgery, cervical radiculopathy or myelopathy, and physical therapy treatments in the last six months before baseline assessment.

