### Description of the developed smartphone app

The smartphone app is designed using Android Studio and Flutter. It integrates advanced features, including an intuitive interface and an easy-to-use solution for all users (***i.e.,*** patients and healthcare professionals). Each participant in the IG will receive a code and password to log into the app and to register some general information such as age and sex. All assigned authentications will be recorded in a database created by Firebase. The app features several integrated modules:

(i) Basic information about NP and ergonomic advice on proper neck position during daily work,(ii) Series of evaluation questions including pain assessment (PI-NRS) and the impact of NP on participant’s daily functioning,(iii) Appropriate sets of exercises with videos and instructions,(iv) Daily reminder feature to prompt users to engage in their prescribed exercises consistently, and(v) Evaluation report providing feedback on user’s state and tracking their adherence.

To record participants’ engagement with the program, adherence will be monitored using a user activation tracking system assessing the frequency and duration of app use. The application is linked to the Cloud and Firebase tool enabling the therapist to visualize participants’ results in a graphical form. Exercises included are automatically adapted at each use of the app according to the participant’s condition and evolution. Indeed, the app is designed to analyze the data collected before each use from the evaluation questions based on an AI algorithm and to provide personalized exercise recommendations. To monitor and ensure participant engagement, app usage analytics will be utilized to track interaction patterns and identify any drop-offs in usage. Participants will also have access to technical support to troubleshoot any issues with the app, ensuring minimal disruption. Additionally, scheduled check-ins with participants will be conducted to address potential barriers to engagement and encourage continued adherence to the intervention protocol.

The diagram block (Fig 3) illustrates the app, which is composed of distinct therapist and participant interfaces.

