### Participant timeline

Participants will be assessed at 4 and 12 weeks. A schematic diagram for participants’ timeline is shown in Fig 1.

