### Methods: Data collection, management, and analysis

#### Plans for assessment and collection of outcomes.

Evaluations will be made at baseline, at the end of the intervention period (fourth week), and at 12 weeks follow up. All evaluations will be performed digitally through a questionnaire where participants will be invited to self-report their level of pain (PI-NRS), their functional disability (NDI), their QoL (SF-12), and to rate their adherence to exercises. At the baseline education session, questionnaires and evaluation tools will be explained to participants to resolve any doubt while answering.

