#### Plans to promote participant retention and complete follow-up.

Daily notifications will be intended to promote participant retention. Participants will also be given a phone number and will be informed that they can call the principal investigator if ever a doubt or a misunderstanding with their intervention protocol occurs. This availability may help participants completing the follow-up. Moreover, participants using the smartphone app will benefit from additional methods to promote self-monitoring and self-management. The information included in the app may also help to encourage participants to complete the study.

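### The non-serious harms the protocol expects are not asked about in either arm, and between scheduled assessments symptoms are described as observed only in the app arm

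*Protocol article*

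**What the plan says.** Under Data monitoring (Harms), the article names what it expects: "No adverse events are anticipated, aside from potential temporary minor discomfort or fatigue". The only action that follows concerns serious events: "should any serious adverse events occur during the trial, the principal investigator would promptly report them to the Ethics Committee".

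Under Plans for assessment and collection of outcomes, the data collection for both arms is described: "All evaluations will be performed digitally through a questionnaire where participants will be invited to self-report their level of pain (PI-NRS"; the list continues with "their functional disability (NDI), their QoL (SF-12), and to rate their adherence to exercises". The common times after baseline are given under Participant timeline: "Participants will be assessed at 4 and 12 weeks". Neither Outcomes nor Statistical methods includes a harm outcome.

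Under Description of the developed smartphone app, the app asks about pain and daily functioning, and "the app is designed to analyze the data collected before each use from the evaluation questions". The therapist can view these results as graphs. The same section announces scheduled check-ins, aimed at engagement. No counterpart is described for the paper arm. Participants are given a phone number so that "they can call the principal investigator if ever a doubt or a misunderstanding with their intervention protocol occurs".

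**The concern.** The protocol identifies two expected harms and then sets no way of counting them. An event that is neither serious nor volunteered leaves no record. In the app arm there is frequent contact through which discomfort or worsening can surface. In the paper arm the described contact between assessments is a phone line that the participant must choose to use, and its stated purpose is doubts about the protocol. Daily notifications go to both arms but are not described as asking anything.

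Two things are at stake. First, the trial could not report how often either programme produces the discomfort or fatigue it anticipates. That matters because the app adapts the exercises automatically while the paper sheet is fixed, so tolerability is a natural question, and the Discussion looks ahead to use in workplaces and among neck pain patients generally. Second, if the final report describes minor events from whatever sources happen to exist, the arm that is watched more closely may look worse for that reason alone. Events that were never asked about cannot be recovered at the analysis stage.

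**Working it through.** The plan states no figure for harms, so there is none to reproduce. The check compares what is asked in each arm and then sizes the imbalance.

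**Step 1. Sources of harm information described in the article**

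| Source | App arm | Paper arm |
|---|---|---|
| PI-NRS, NDI, SF-12, adherence at weeks 4 and 12 | yes | yes |
| Discomfort, fatigue or adverse-event item in that questionnaire | none listed | none listed |
| Pain and function questions before each use | yes | not described |
| Therapist view of those answers | yes | not described |
| Scheduled check-ins (described in the app section, for engagement) | yes | not stated |
| Phone line for doubts about the protocol | yes | yes |
| Reporting of pain medication | yes | yes |
| Escalation of serious adverse events | yes | yes |

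The second row shows that solicitation is missing in both arms. Rows three to five show where observation is unequal.

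**Step 2. Frequency of symptom enquiry**

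Inputs: three to five exercise days per week for 12 weeks (Intervention description); questions before each app use; two common assessments after baseline.

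- App arm, full adherence: 3 × 12 = 36 to 5 × 12 = 60 sets of questions per participant, in addition to the two common assessments.
- Paper arm: the two common assessments.

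The 36 to 60 is a ceiling set by full adherence. The section on collection of outcomes also calls week 4 the end of the intervention, which conflicts with the 12-week programme; the two sections must be reconciled. If exercise ended at week 4, the range would be 3 × 4 = 12 to 5 × 4 = 20.

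**Step 3. What unequal detection could do (all rates assumed)**

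Expected recorded cases = 25 × true rate × probability of detection, with 25 per arm from the Sample size section. Take the same true rate of 20% in both arms.

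- App arm, detection 90%: 25 × 0.20 × 0.90 = 4.5 cases.
- Paper arm, detection 50%: 25 × 0.20 × 0.50 = 2.5 cases; difference 0.20 × (0.90 − 0.50) = 8 percentage points.
- Paper arm, detection 30%: 25 × 0.20 × 0.30 = 1.5 cases; difference 0.20 × (0.90 − 0.30) = 12 points.

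For true rates from 10% to 30%, with the same detection values, the spurious difference runs from 0.10 × 0.40 = 4 points to 0.30 × 0.60 = 18 points. With equal detection it is zero.

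**Step 4. What the trial could say if harms were asked about**

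If no event is recorded among n participants who were all asked, the one-sided 95% upper limit on the rate is 1 − 0.05^(1/n).

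- n = 25: 11.3%.
- n = 22 (10% loss: 25 × 0.9 = 22.5, rounded down): 12.7%.

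These limits need solicited data. They do not measure the defect; they show what common items would allow the trial to state.

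**The case against.** The strongest reply has four parts.

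**Both arms are observed.** A reader might infer that worsening during treatment can be seen only in the app arm. The documents do not support that. Both arms report PI-NRS, NDI and SF-12 at week 4, which lies within the 12-week programme, and again at week 12. Medication reporting and the phone line are not confined to one arm. The imbalance concerns the periods between assessments.

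**No harm comparison is planned.** A reader might infer that any harm comparison would be empty or biased. That goes too far. Neither Outcomes nor Statistical methods contains a harm analysis, so no planned analysis is biased. Worsening on PI-NRS or NDI at weeks 4 and 12 could be compared with the same instrument at the same times, subject to the fact that participants are not blinded. Nothing says that app readings will feed outcomes or event counts.

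**The article is condensed.** An adverse-event form may exist in a full protocol that is not shown. This stands as a caution, and silence alone would not carry the point. But the article does list the contents of the common questionnaire, does name expected harms, and does describe contact that differs by arm. NDI or SF-12 items might touch on fatigue; the documents do not list the items, so this cannot be settled either way.

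**The risk is low.** For neck exercises in one workplace, with the same investigator responsible for both arms, omitting a monitoring committee is reasonable. That does not explain leaving the expected events uncollected. It is conjecture, though, that a serious event would go unheard of in the paper arm, and the point does not rely on it.

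A reader might also see a conflict between the exclusions under Eligibility criteria ("spine trauma or surgery, cervical radiculopathy or myelopathy") and the section on discontinuing interventions. There is none: one governs entry, and the other says that requests to withdraw will be accommodated.

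**Conclusion.** The point holds as a defect in how harms are ascertained. As written, the protocol names discomfort and fatigue, asks about neither in the common questionnaire, and describes observation between assessments in the app arm only. Any account of non-serious events based on app data, check-ins or spontaneous reports would be exposed to unequal detection.

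The imbalance is at most about 36 to 60 app enquiries against two common assessments, assuming full adherence for 12 weeks. A spurious difference of 4 to 18 percentage points is possible under the assumed rates and detection probabilities; this is an illustration and not an estimate. The efficacy outcomes at weeks 4 and 12 are untouched. The conclusion assumes that the article's list of questionnaire contents is complete and that no harm form sits in an unseen full protocol. It is an inexpensive improvement, worth making before recruitment because it cannot be made afterwards.

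**What to change.** 1. Add the same short harm items to the existing week 4 and week 12 questionnaires in both arms: new or worse symptoms, discomfort, fatigue, and care sought.
2. State in the Harms paragraph that any between-arm description of harms uses only these common items.
3. State that symptom data collected only through the app, or through app-arm check-ins, are reported separately and are not compared with the paper arm.

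The cost is a slightly longer digital form that already goes to every participant, some minor events to review, and the ethics committee review that the Protocol amendments section requires for changes. The sample size and the efficacy analysis do not change.

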### Ethics and dissemination

#### Research ethics approval.

The study protocol has the approval of the Ethics Committee of the Faculty of Medicine of Monastir, Tunisia (IORG 0009738 N°182 OMB 0990−0279) and has been registered in ClinicalTrials.gov under the identification number NCT06485804.

#### Protocol amendments.

We do not anticipate any significant protocol modifications. However, if any changes do occur, they will need to undergo review by the Ethics Committee of the Faculty of Medicine of Monastir (Tunisia).

## Discussion

The current project will evaluate the effectiveness of a smartphone app consisting of personalized neck exercises, when compared with a conventional approach for self-rehabilitation. We expect that this innovative approach will have immediate and short-term positive effects on pain, function and QoL of office workers suffering from chronic NP. Moreover, this approach is expected to resolve the problem of adherence to self-exercises in this chronic condition.

These positive outcomes may be applicable not only to office workers with NP, but also to all NP patients. The app is a new way to treat and monitor patients’ symptoms and evolution, using new technology that facilitates constant patient-therapist communication. The integration of AI allows for dynamic adjustments based on individual progress, preferences, and real-time feedback, making the rehabilitation process more engaging and tailored to the user’s specific needs [38]. Additionally, the user-friendly interface of smartphone apps facilitates easy access to exercises, promoting greater compliance and consistency [39]. External factors such as participant motivation, technical issues with the app, and the required frequency of notifications may influence adherence to smartphone-guided exercises. To address these challenges, interventions should focus on designing user-friendly applications, providing personalized reminders, and incorporating motivational strategies such as feedback or gamification. These approaches have been suggested to improve adherence to technology-based health interventions in similar contexts [40]. Embracing these advancements in technology holds the potential to revolutionize the landscape of rehabilitation self-exercises, offering patients effective and accessible tools to actively participate in their recovery [41]. A key strength of smartphone-guided exercises is their ability to adapt to individual needs and preferences. The app’s personalized features can dynamically adjust exercise intensity, frequency, and duration based on user feedback and progress. By continuously monitoring user performance and providing real-time feedback, the app can optimize the rehabilitation program to maximize its effectiveness. This level of personalization can significantly improve adherence and motivation, leading to better outcomes in the long term [39]. Research has shown that using these tools is effective on pain, function, posture and QoL in office workers with NP [26,42] and in patients with NP in general [43]. Moreover, it has been shown that such an AI-embedded smartphone app increased the time spent on therapeutic exercise; reduced pain levels and decreased the need for other interventions in both NP and back pain [44]. Similarly, significant improvements in these conditions and in shoulder pain after using an AI-assisted health program in office workers has been reported [45]. By implementing interventions reported to have positive impact in NP within the workplace, corporations are testifying of their growing commitment to employee well-being and are anticipating benefits of cost reduction linked with absenteeism and presentism and enhancing productivity linked with a healthier workforce [46]. These interventions are gaining significance in alleviating the impact of a pathology known to occur within a work duration ≥ 5 years in office computer users independently of other risk factors [47]. The use of digital tools may also have the potential to generate positive impact on healthcare quality [48] and on healthcare systems in general by reducing direct costs (***i.e.,*** lowering face-to-face consultations, preventing unnecessary control visits), and indirect costs (***i.e.,*** patient travel, and work leaves) [49]. Findings from this study could directly inform workplace wellness policies by encouraging employers to integrate smartphone-guided exercise programs as cost-effective and accessible interventions to reduce NP among office workers. Such programs could promote regular physical activity, potentially improving productivity and reducing healthcare costs associated with musculoskeletal complaints. Clinically, these findings may support the use of digital health tools as an adjunct to standard care for NP management, aligning with evidence suggesting that technology-based interventions are effective for musculoskeletal disorders [49]. This will highlight their potential for scalable, real-world application in both occupational and healthcare settings.

### Study limitations

A notable limitation of this study could be its relatively brief follow-up period of 12 weeks. Extending the follow-up duration could offer greater insights into efficacy and participant adherence over a longer period. Subsequent studies should take this into account to comprehensively assess effectiveness and participant commitment over extended periods. Another limitation is the potential bias introduced by varying levels of participants’ familiarity with mobile apps and technology literacy, which could influence adherence rates. Future studies should consider stratifying participants by technology proficiency or providing standardized training to minimize these biases. Additionally, the assessment of the cost-effectiveness of the intervention proposed in this study will not be undertaken.

## Conclusion

In summary, by addressing the specific issue of NP associated with daily computer use, the study findings could help to get a better understanding of how to deliver self-care strategies for office workers with this chronic painful condition, and to develop evidence-based knowledge about the impact of workplace interventions using new technologies in mitigating discomfort and promoting well-being among affected workers.

## Abbreviations

AI: artificial intelligence
app: application
CG: control group
IG: interventional group
NDI: neck disability index
NP: neck pain
PI-NRS: pain intensity number rating scale
QoL: Quality of life
QoWL: quality of work life
SF12: short form 12.
